### Randomisation

Biomedical statisticians at our institution's Dept. of Public Health have arranged for a computer generated random number sequence, of unspecified block size stratified for parity. This randomisation plan will produce study arms of approximately equal size with similar numbers of nulliparous and multiparous participants.

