#### Power calculation

It is proposed that sufficient women be randomised to provide reliable evidence of the effects of antenatal hypnosis regarding the primary outcome measure of this study: the incidence of not using pharmacological pain relief during labour. An audit of 100 consecutive mothers birthing at the Women's and Children's Hospital in May 2004 showed an incidence of using one or more pharmacological interventions of 80%. In order to show a clinically relevant fall of 20% in the number of women requiring pharmacological analgesia ie from 80% to 64%. Using a 2 tailed calculation (Nquery advisor computer program V.5) a study with 80% power would require each group to contain 135 women to detect this difference at the 0.05 level.

Complete collection of the primary endpoint is likely as all analgesia techniques used such as Entonox, pethidine and epidural analgesia are documented routinely in the labour ward birth register and medical record by the woman's treating midwife. We plan to recruit 150 women/group as we estimate that 10% of participants' will deliver prior to receiving their allocated treatment. The findings of our case matched control study at the Women's and Children's Hospital[47] are consistent with those of our systematic review of the literature on this topic [22]. No comparative trials have investigated the effects of hypnosis on the incidence of postnatal depression although acknowledged experts in the field report a low incidence in women taught hypnosis (<1%) [21]. The prevalence of post-natal depression in several recent studies in Australia is between 13 and 18% [63]. Our proposed study has a power of 80% at the 0.05 level of significance to show a reduction from 16% to 5.4% for this secondary outcome. For normally distributed continuous measures (eg EPDS) we would be able to detect shifts of 0.4 SD with a power of 80 % between individual arms of the study (n = 135 per group). Comparisons which exploit the two treatment groups (assuming a conservative estimate of postnatal data in 270 subjects in Groups 1 and 2) would have 80% power to detect a shift of only 0.28 SD.

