**[see **Additional file 2**] **for estimated detectable differences in key endpoints with sample size of 135/group. Based on these estimates a total recruitment of 450 women will enable detection of significant differences of clinical relevance for the primary outcome and for some key secondary outcomes. We recognize that a trial of this size may be too small to detect differences in the risk of some of our secondary endpoints but the information will allow comparisons of women in other hypnosis studies in a systematic review or suggest other beneficial outcomes or adverse effects that require further controlled evaluation.

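### The detectable shifts given for continuous outcomes (0.4 SD between arms, 0.28 SD with the hypnosis arms pooled) do not follow from the stated numbers of women and cannot both hold at one alpha and power

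*Protocol article*

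**What the plan says.** The Power calculation section of the protocol article gives two sensitivity statements for normally distributed measures, with the EPDS as the example. Between individual arms the trial can "detect shifts of 0.4 SD with a power of 80 % between individual arms of the study (n = 135 per group". For comparisons that draw on both hypnosis groups, "assuming a conservative estimate of postnatal data in 270 subjects in Groups 1 and 2", the trial "would have 80% power to detect a shift of only 0.28 SD".

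The level is not repeated for these outcomes. The same section describes the primary calculation as "Using a 2 tailed calculation (Nquery advisor computer program V.5", at the 0.05 level, and says of postnatal depression: "Our proposed study has a power of 80% at the 0.05 level of significance".

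On numbers, the section says "We plan to recruit 150 women/group as we estimate that 10% of participants' will deliver prior to receiving their allocated treatment", which is where 135 per group comes from, and puts total recruitment at 450. The Randomisation section says of the arms: "This randomisation plan will produce study arms of approximately equal size". No control number is given for the pooled comparison.

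**The concern.** When two equal arms are pooled and compared with a third arm of the same size, only one side of the comparison doubles. The detectable shift should then fall by a factor of 0.866. The stated figures fall by 0.28/0.4 = 0.70, close to 1/√2 = 0.707, which is what would happen if the control arm doubled as well.

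The mother's emotional well-being is one of the trial's specific aims. It is measured with the EPDS and the Spielberger scales at 6 weeks and 6 months, and these are the power figures a reader would use to interpret a null result on those scales. The between-arm figure undersells the trial and the pooled figure oversells it, so pooling looks more rewarding than it is.

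**Working it through.** **Inputs.** From Power calculation: 135 per arm, 270 in Groups 1 and 2 together, 80% power, shifts in SD units (so SD = 1). From Randomisation: equal arms, hence 135 controls on the planning figure and 150 at most (450/3). Two-sided 0.05 is carried over from the binary outcomes in the same section; this is an assumption.

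**The section's binary figures reproduce.** 80% v 64% needs 123 per group without and 135 with continuity correction, matching the stated 135. For 16% v 5.4% at 135 per group, power is 80.8%, matching the stated 80%. The fault is confined to the continuous figures.

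**Formula.** Detectable shift = (z for alpha + z for power) × √(1/n₁ + 1/n₂). At two-sided 0.05 and 80% power the z-sum is 1.960 + 0.842 = 2.802.

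**Between arms, 135 v 135.**
- Detectable shift: 2.802 × √(2/135) = 0.341 SD (t-test 0.342). Stated: 0.4.
- Power at 0.4 SD: 0.4/√(2/135) = 3.286, less 1.960 = 1.326, giving 90.8% (t-test 90.6%).
- Number needed for 0.4 SD at 80% power: 2 × (2.802/0.4)² = 98.1, so 99 per group.

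**Pooled, 270 v 135.**
- Detectable shift: 2.802 × √(1/270 + 1/135) = 0.295 SD (t-test 0.296). Stated: 0.28.
- Power at 0.28 SD: 0.28/√(3/270) = 2.656, less 1.960 = 0.696, giving 75.7% (t-test 75.5%).
- Number needed for 0.28 SD at 80% power and 2:1: 151 controls and about 302 treated.

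**Other settings tried (normal approximation, SD).**

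| Alpha, power | 135 v 135 | 270 v 135 | 270 v 150 | 300 v 150 |
|---|---|---|---|---|
| Two-sided 0.05, 80% | 0.341 | 0.295 | 0.285 | 0.280 |
| Two-sided 0.05, 90% | 0.394 | 0.342 | 0.330 | 0.324 |
| One-sided 0.05, 80% | 0.303 | 0.262 | 0.253 | 0.249 |
| Two-sided 0.05/3, 80% | 0.394 | 0.341 | 0.330 | 0.324 |

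No row gives both 0.4 and 0.28. The value 0.28 is reached at 300 v 150, which means no postnatal data lost and conflicts with calling 270 conservative.

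**A check that does not depend on alpha or power.** If both figures share one z-sum, it cancels from their ratio.
- 135 v 135 against 270 v 135: √(2/135)/√(1/270 + 1/135) = 1.155.
- Against 270 v 150: 1.195. Against 300 v 150, the largest the design allows: 1.217.
- Stated: 0.4/0.28 = 1.43. With rounding as generous as possible: 0.35/0.285 = 1.228.

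Even the most favourable rounding lies above the largest ratio the design allows. Put the other way, the stated figures imply z-sums of 3.29 (between arms) and 2.66 (pooled), on either side of 2.80.

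**The case against.** The strongest defence is that the section states neither the control number for the pooled comparison nor the level for continuous outcomes. The 10% loss is of women who deliver before receiving their allocated treatment. Group 3 receives none, so all 150 controls might be available. The pooled figure is then 0.285 SD (t-test 0.286), and power at 0.28 SD is about 78%, close to a rounding difference. If the three between-arm tests were each run at 0.05/3, 135 v 135 gives 0.39 to 0.40 SD, and a single pooled test might be left at 0.05. Additional file 2, which is not shown, might explain the basis. Finally, 0.4 SD errs on the safe side, and these figures did not set the sample size.

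Part of this stands. The control number and the level are assumptions, the discrepancy in the pooled figure is small, and 0.4 SD is true as a statement of at least 80% power. But the rescue needs a corrected level for one figure, an uncorrected level for the other and a control arm without losses. The article states none of these, and it uses 135 for every arm in the between-arm figure. Even then the pooled result is 0.285 to 0.286, not 0.28. Additional file 2 is described as covering 135 per group, so it could disclose a mixed basis but could not bring the two figures onto a common one.

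**Conclusion.** The concern holds. At two-sided 0.05 and 80% power the detectable shifts are 0.34 SD for 135 v 135, not 0.4, and 0.30 SD for 270 v 135, not 0.28. Actual power is about 91% at 0.4 SD and about 76% at 0.28 SD. Pooling reduces the detectable shift by about 13%, where the stated figures imply 30%.

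The corrected values rest on two assumptions: that two-sided 0.05 applies to the continuous outcomes, and that 135 controls have data. With 150 controls the pooled value is 0.285. The mutual inconsistency rests on neither, only on the two figures sharing one alpha and power. How 0.28 arose is not stated; division of 0.4 by √2 would produce it, but that is inference.

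The effect is limited to secondary continuous outcomes. The primary sample size is unaffected, and only the pooled figure errs in the optimistic direction.

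**What to change.** In Power calculation, replace 0.4 SD with 0.34 SD (135 v 135) and 0.28 SD with 0.30 SD (270 v 135), and state the level (two-sided 0.05), the power (80%) and the control number beside them.

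If 0.4 was meant at 90% power or at a level divided by three, say so and give the pooled figure on the same basis, which is 0.34 SD. If the two comparisons are deliberately held to different levels, or all 150 controls are assumed to have data, state that and recompute the pooled figure accordingly.

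The cost is two numbers and a clause. Recruitment, design and analysis do not change; the pooled claim becomes slightly less favourable.

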**Methods/design:**

A single centre, randomised controlled trial using a 3 arm parallel group design in the largest tertiary maternity unit in South Australia. Group 1 participants receive antenatal hypnosis training in preparation for childbirth administered by a qualified hypnotherapist with the use of an audio compact disc on hypnosis for re-enforcement; Group 2 consists of antenatal hypnosis training in preparation for childbirth using an audio compact disc on hypnosis administered by a nurse with no training in hypnotherapy; Group 3 participants continue with their usual preparation for childbirth with no additional intervention. Women > 34 and < 39 weeks gestation, planning a vaginal birth, not in active labour, with a singleton, viable fetus of vertex presentation, are eligible to participate. Allocation concealment is achieved using telephone randomisation. Participants assigned to hypnosis groups commence hypnosis training as near as possible to 37 weeks gestation. Treatment allocations are concealed from treating obstetricians, anaesthetists, midwives and those personnel collecting and analysing data. Our sample size of 135 women/group gives the study 80% power to detect a clinically relevant fall of 20% in the number of women requiring pharmacological analgesia – the primary endpoint. We estimate that approximately 5–10% of women will deliver prior to receiving their allocated intervention. We plan to recruit 150 women/group and perform sequential interim analyses when 150 and 300 participants have been recruited. All participant data will be analysed, by a researcher blinded to treatment allocation, according to the "Intention to treat" principle with comprehensive pre-planned cost- benefit and subgroup analyses.

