#### Further follow up

Postnatal questionnaires will be sent to each participant at 6 weeks and 6 months after the birth where the EPDS[61] and Spielberger anxiety scales[60] will be repeated. Women will be asked whether they are still breast feeding and invited to make comments of any problems or difficulties with the intervention. Two weeks after postage of postnatal questionnaires there will be follow-up by telephone call at home for non-responders.

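### The counts of 135 and 270 women with postnatal data come from an early-birth margin: depression power needs about 89% questionnaire return, and the pooled 0.28 SD figure allows for no loss

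*Protocol article*

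**What the plan says.** All statements are in the protocol article.

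- **Sample size and margin.** In the Power calculation section, "Using a 2 tailed calculation (Nquery advisor computer program V.5) a study with 80% power would require each group to contain 135 women" for the primary outcome. The same section then says: "We plan to recruit 150 women/group as we estimate that 10% of participants' will deliver prior to receiving their allocated treatment". The abstract gives the same reason with a range: "We estimate that approximately 5–10% of women will deliver prior to receiving their allocated intervention". No other reason for the extra 15 women per group is given.
- **Primary outcome data.** The Power calculation section says "Complete collection of the primary endpoint is likely", because analgesia is routinely recorded in the birth register and medical record.
- **Postnatal outcomes.** The same section claims 80% power for a fall in postnatal depression from 16% to 5.4%, for a 0.4 SD shift between single arms at 135 per group, and for a 0.28 SD shift in comparisons using both hypnosis groups, "assuming a conservative estimate of postnatal data in 270 subjects in Groups 1 and 2".
- **How those data arrive.** Under Further follow up: "Postnatal questionnaires will be sent to each participant at 6 weeks and 6 months after the birth". Non-responders are telephoned. No expected return rate is given.
- **Who is followed and analysed.** The section on compliance with treatment schedules gives all randomised women the same postpartum follow-up, whatever treatment they received. The Analyses section applies intention to treat to primary and secondary outcomes.

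**The concern.** Early birth and an unreturned questionnaire are different events. A woman who gives birth before her first session still has a birth-register entry and is still sent the questionnaires. She costs power by diluting the treatment effect. A woman who does not return the form costs power because her depression outcome is missing. The plan has one 10% margin, explained only by the first event, and uses the resulting 135 and 270 as the number of women with postnatal data. It calls this conservative without a return rate to support the word.

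At stake is how the depression result is read. The Discussion calls the incidence of postnatal depression a key endpoint, and the plan attaches an explicit 80% power to it. If returns fall short, or early births weaken the contrast, a null result could be taken as adequately powered when it is not.

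**Working it through.** **Inputs from the article.** Two-sided 0.05; 135 needed and 150 recruited per group; 10% early births; depression 16% v 5.4%; EPDS shifts of 0.4 SD (single arms) and 0.28 SD (Groups 1 and 2 together). **Assumptions not in the article.** Returns of 90%, 80% and 70%; comparison of Groups 1 and 2 together with Group 3; a normal approximation throughout.

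**1. The margin.** 135/(1 − 0.10) = 150, and 270 = 2 × 135 = 90% of 300. The early-birth allowance accounts for the whole step, and the postnatal count is the same number.

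**2. Reproducing the depression figure.** Power = Φ{[d − 1.96·√(2p̄(1 − p̄)/n)] / √[(p₁q₁ + p₂q₂)/n]}, with d = 0.16 − 0.054 = 0.106 and p̄ = 0.107. At n = 135: (0.106 − 1.96 × 0.03762)/0.03707 = 0.870, so power is 80.8%. The plan's 80% is reproduced. The smallest n that gives 80% is 133, and 133/150 = 89%. (This is the uncorrected formula. With a continuity correction, which is what reproduces the 135 for the primary outcome, depression would need 151 per arm.)

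**3. Checking the pooled EPDS figure.** Detectable shift = (1.96 + 0.8416)·√(1/n₁ + 1/n₂).

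- 270 v 135: √(1/270 + 1/135) = 0.1054, so the shift is 0.295 SD. Power at 0.28 SD is Φ(0.28/0.1054 − 1.96) = Φ(0.696) = 75.7%.
- 300 v 150: √(1/300 + 1/150) = 0.1000, so the shift is 0.280 SD and power is 80.0%.
- 270 v all 150 controls: √(1/270 + 1/150) = 0.1018, so the shift is 0.285 SD and power is Φ(0.790) = 78.5%.

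The stated 0.28 SD is therefore not reproduced at 270 v 135. It matches all recruited women with no loss. It is also close to 0.4/√2 = 0.283, which may be where it came from, but that is a guess.

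**4. Checking the pairwise EPDS figure.** At 135 per arm, √(2/135) = 0.1217 and power at 0.4 SD is Φ(0.4/0.1217 − 1.96) = 90.8%. 80% power needs only 99 per arm, or 66% of 150.

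**5. Range of returns, taken from 150 per arm.**

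| Return | Forms per arm | Depression, 16% v 5.4% | Pooled, power at 0.28 SD | Pooled, detectable shift | Pairwise, power at 0.4 SD |
|---|---|---|---|---|---|
| 100% | 150 | 84.7% | 80.0% | 0.280 SD | 93.4% |
| 90% | 135 | 80.8% | 75.7% | 0.295 SD | 90.8% |
| 80% | 120 | 76.0% | 70.7% | 0.313 SD | 87.3% |
| 70% | 105 | 70.3% | 64.9% | 0.335 SD | 82.6% |

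**6. Dilution by early births.** If 10% of the hypnosis arm have no effect, their rate stays at 16% and the arm's rate is 0.9 × 5.4% + 0.1 × 16% = 6.46%. Power for 16% v 6.46% is 74.7% at 150 per arm and 70.1% at 135.

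**The case against.** A reader might infer that the plan has no allowance for non-return at all, or that 135 per arm requires every form to come back. The documents do not support this. Early deliverers are followed identically and analysed as randomised, so early birth removes no questionnaire. With 150 randomised, 135 with postnatal data means 90% return. That objection stands: a 10% allowance is implied, though not named or justified.

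A reader might also infer that every EPDS power statement fails. The pairwise 0.4 SD claim does not: it still holds at 70% return.

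Nor do the documents show that 90% return is unrealistic. They give no return rate, and non-responders are telephoned. What can be said is that the word conservative has nothing behind it.

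Other points carry some weight. The loss for depression is moderate: 76% instead of 80% at 80% return. If depression were compared between both hypnosis groups together and usual care, the same formula gives 91%, 88% and 84% at 90%, 80% and 70% return. But the stated 80% matches the single-arm comparison, and the pooled comparison is offered only for continuous measures. The 16% to 5.4% contrast may already be meant as the effect in all randomised women, in which case step 6 falls away; the plan does not say. Finally, these are secondary outcomes, the article concedes that some may be underpowered, and Additional file 2, which holds detectable differences, is not shown. None of this makes 0.28 SD agree with 270 v 135.

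**Conclusion.** The point holds in a limited form. One margin, explained only by early births, also serves as the count of women with postnatal data.

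- **Depression.** The 80% holds only if about 133 of 150 women per arm (89%) return the form and early births do not dilute the effect. It falls to 76% and 70% at assumed returns of 80% and 70%, and to about 70% at 135 per arm if 10% of the hypnosis arm get no effect.
- **Pooled EPDS.** This is an arithmetic mismatch that needs no assumed return rate: 0.28 SD has 75.7% power at 270 v 135. It does assume that the comparison group is usual care with 135 women, but even all 150 controls would not bring it to 80%.
- **Pairwise EPDS.** The 0.4 SD statement is sound and understates the power.

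The primary outcome does not depend on questionnaires and is not touched.

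**What to change.** In the Power calculation section:

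1. State the assumed questionnaire return at 6 weeks and at 6 months, separately from the early-birth allowance. Say whether the 16% to 5.4% contrast is the effect in all randomised women or only in those who receive the sessions.
2. Give depression power at 90%, 80% and 70% return of 150 per arm: 81%, 76% and 70%.
3. Correct the pooled detectable shift to 0.295 SD for 270 v 135, and add 0.313 SD at 80% return and 0.335 SD at 70%.
4. Delete the word conservative.

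The cost is slightly less favourable stated figures for secondary outcomes. No more patients are needed, and no procedure changes.

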### Data collection and outcomes

Our primary outcome the use of pharmacological analgesia during labour and childbirth will be collected from the birth register where all analgesia is documented by the attending midwife. Any unclear entries will be clarified by referring to the medical and midwifery record of the birth. Most of our key secondary endpoints such as the use of oxytocics, the mode of delivery, neonatal Apgar score at 5 minutes < 7 and maternal admission to the High Dependency Unit (HDU) or the Intensive Care Unit (ICU) will be obtained from the birth register. These outcomes will have been documented by the attending midwife who will be unaware of the parturient's group allocation. A second researcher who is blinded to treatment allocation will manage data collections on the ward and from post-natal questionnaires. Details of maternal side effects will be collected such as; PPH=>600 mls; blood transfusion; death; ICU admission, meconium stained liquor; babies admitted to neonatal unit. Mothers will be asked to complete a postpartum questionnaire while in hospital and asked to rate the overall pain experienced during labour and childbirth, whether the birth experience was: Worse/better/same as expected, whether they felt in control during the labour during the birth and whether the birth was rated a positive or negative experience. We will also ask: how well the mother felt she coped with labour and childbirth; whether hypnosis training was obtained outside the trial; and whether hypnosis will be used in future pregnancies. Length of neonatal nursery stay, length of maternal stay in hospital and the number of women breast feeding at discharge from hospital will also be recorded.

#### Further follow up

Postnatal questionnaires will be sent to each participant at 6 weeks and 6 months after the birth where the EPDS[61] and Spielberger anxiety scales[60] will be repeated. Women will be asked whether they are still breast feeding and invited to make comments of any problems or difficulties with the intervention. Two weeks after postage of postnatal questionnaires there will be follow-up by telephone call at home for non-responders.

### Data management, proposed analyses and reporting of results

#### Data management

The Expected Date of Confinement (EDC) of each participant recruited is entered on an Excel spreadsheet and a register of trial participants is accessed from our hospital patient database (OACIS) on a daily basis on order to identify when a trial participant has delivered. The date of delivery is entered on the spreadsheet which then utilises calculated fields to indicate when 6 week and six month postnatal surveys are due. Data entry onto a computer database, data verification and completion of all data fields will be finalised as early as possible at each time point that the data becomes available. All data will be accounted for and reasons given for why any data is missing.

